### Patient and public involvement

Patients nor public have been involved in the design, conduct, reporting or dessimination plans of our research. The feasibility and exploratory nature of this trial and the specifics of the interventions do not facilitate an opportunity or need to do so.

### Inclusion criteria

#### Part A

Healthy volunteers must meet all of the following criteria for eligibility: they must be aged 18–55 years and demonstrate willingness and capability to adhere to study protocols. Participants must exhibit good overall health as determined by the investigator, based on comprehensive assessments including vital signs, medical history, physical examination, and laboratory evaluations. Furthermore, subjects are required to have a body mass index ranging from 18 to 32 kg/m^2^, with a minimum body weight of 50 kg. Additionally, participants must be surgically sterile, post-menopausal, or pre-menopausal with a negative urine pregnancy test at screening, and if pre-menopausal and not surgically sterile, must agree to employ effective contraception. Normal electrocardiography (ECG) and clinical laboratory findings are requisite, with any deviations considered clinically insignificant. Negative results for both drug and alcohol screenings are mandatory. Finally, a subject must have adequate healthy skin surface area on the forearm (>100 cm^2^) for study procedures.

#### Part B

Breast cancer patients must be aged 18 years or older at screening and be willing and able to adhere to study procedures. Patients must have a confirmed diagnosis of invasive breast cancer and/or grade III ductal carcinoma *in situ* (DCIS), with a total tumour diameter ≥ 5 cm, with scheduled breast-conserving surgery at the Leiden University Medical Center. Normal 12-lead ECG and clinical laboratory results are required, with any deviations deemed clinically insignificant at the investigator's discretion. Patients must be surgically sterile, post-menopausal, or pre-menopausal with a negative urine pregnancy test before receiving AKRO-6qcICG. Pre-menopausal patients who are not surgically sterile must commit to employing effective contraception for a minimum of 30 days after their final dose of study treatment. For both Part A and B, written informed consent, in accordance with ICH/GCP and national/local regulations, is obligatory prior to engagement in any study-related activities.

### Exclusion criteria

#### Part A

Exclusion criteria for Part A include any history or presence of clinically significant medical conditions or abnormalities as determined by the investigator, based on physical examination, laboratory test results (including hepatic and renal panels, complete blood count, and urine dipstick), or ECG at screening. If uncertainty arises from screening tests, additional evaluations may be conducted to confirm eligibility or deemed irrelevant by the investigator for healthy subjects. Moreover, individuals with a history of skin disease or existing skin conditions that could impede study assessments are excluded. Furthermore, subjects with tattoos, scratches, open sores, excessive hair, or skin damage in the treatment area(s) that may interfere with evaluations are ineligible. Additionally, individuals with Fitzpatrick's Skin Phototype ≥4, recent sun exposure, planned sun exposure, or use of tanning booths within four weeks prior to AKRO-6qcICG administration are excluded. Laser treatment or electrolysis on application areas within four weeks prior to administration or planned during the study period renders subjects ineligible. Shaving of the application area 72 h before administration or planned during the study period is grounds for exclusion. Likewise, recent use of topically applied treatments on the targeted area(s) within one week prior to administration is disqualifying. History of hypertrophic scarring or keloid formation, recent anticoagulant medication use, pregnancy, lactation, positive screening for hepatitis B, hepatitis C, or human immunodeficiency virus, recent prescription medication or substance use that may influence study outcomes, prior inclusion in this study, recent participation in a clinical trial, recent alcohol consumption, positive urine drug screen or alcohol test, history of anaphylactic reactions to medication or supplements, recent blood loss or donation over 500 mL, or any other condition that, in the investigator's opinion, would complicate or compromise the study or subject well-being, are grounds for exclusion.

#### Part B

In Part B, patients who exhibit a radiologic complete response of the primary tumour (rCR) following neoadjuvant therapy, those with a history of surgery and/or radiation on the ipsilateral breast, or individuals with a history of clinically significant allergies or anaphylactic reactions will be excluded. Additionally, patients with conditions that, in the investigators’ judgment, may compromise patient well-being or study objectives are ineligible. Furthermore, exclusion extends to patients with hyperthyroidism defined by TSH levels < 0.15 mU/l and free T4 levels > 24.0 pmol/l, impaired renal function defined by eGFR < 50 mL/min/1.73m2, or impaired liver function defined by values exceeding 3 times the upper limit of normal (ULN) for ALT, AST, or 2 times the ULN for total bilirubin. Participation in another clinical trial where the patient receives a fluorophore perioperatively, lactation, pregnancy, or any psychological, familial, sociological, or geographical condition that may hinder compliance with the study protocol and follow-up schedule are also grounds for exclusion.

### Study drug

AKRO-6qcICG, the sterile lyophilized Drug Product and the sterile 19.5% w/v Poloxamer-407 thermosensitive gel were manufactured in the department of Clinical Pharmacy and Toxicology, Leiden University Medical Center, according to cGMP. The study drug consists of AKRO-6qcICG Drug Product, reconstituted on the day of use in DMSO and diluted in in the thermosensitive poloxamer gel, with a final concentration of 3.5% DMSO in the study drug gel. AKRO-6qcICG is a small organic molecule whose structure is composed of both a NIR dye indocyanine green (ICG) and a non-fluorescent quencher moiety (IRDye QC-1) covalently bound to a dipeptide scaffold. 6qc-ICG is a fluorescently quenched, cathepsin-activatable imaging agent. The vehicle gel part of the study drug is composed of 19.5% w/v Poloxamer 407 solution in water for injections. Poloxamer 407 is a triblock copolymer containing a central hydrophobic polyoxypropylene block flanked by a hydrophilic polyoxyethylene (PEG) block at either end. Such poloxamers have the general formula O(C2H4O)x(C3H6O)y(C2H4O)zH. At low temperatures the polymer strands are highly solubilized by extensive hydrogen bonding to water molecules and the solution is relatively free flowing. At higher temperatures the hydrophobic fragments (polyoxypropylene blocks) aggregate to a much higher degree, leading to the exclusion of water molecules and subsequent spherical micelle formation. This results in gelation of the solution, which is reversible as the temperature decreases and the polymer strands are once again solubilized by hydrogen bonding with water molecules. The gel transition temperature is dependent on the poloxamer concentration. The concentration of 19.5% w/v Poloxamer-407 was based upon measurements of representative surgical breast cavity surface temperature during regular procedures by way of a hand-held IR temperature measurement gun (21, 22). 6qc-ICG is stable in the presence of acids, bases and metal ions.

### Intervention

Part A will include one day for screening, one treatment period of approximately 8 h and two blister evaluation visits, three and 12 days post-dosing. To mimic a surgical wound, four circular application areas of approximately 2 cm in diameter (corresponding to the wound area of approximately 1 cm in diameter and approximately 0.5–1 cm in diameter of the surrounding area) will be made on the skin of the forearm of a healthy volunteer using a blister suction device (NP-4, Electric Diversities, Maryland, USA). By using negative pressure, the device induces a 10 mm diameter painless blister in approximately 60–90 min. The roof of the formed blister is pierced with a needle and the blister fluid is aspirated. Then the blister roof, i.e., epidermal sheet, will be harvested. The four areas will be denoted as ‘Area 1’, ‘Area 2’, ‘Area 3’, ‘Area 4’. Treatments will be applied directly to the blister wounds and the surrounding skin. The four treatment conditions (AKRO-6qcICG 50 µM = 0.115 mg/l, AKRO-6qcICG 25 µM = 0.0575 mg/l, vehicle (placebo), untreated) will be randomized by computer to the four treatment areas. Both the investigator and the healthy volunteer will be blinded through sealed syringes. The assigned treatment will be applied directly onto approximately 1 cm of wounded skin and approximately 0.5–1 cm in diameter of the surrounding area. A minimum of 5 cm distance will be achieved between wounded skin. Pharmacokinetic (PK) blood and urine sample collection, local and systemic tolerability assessment, clinical wound assessment, and clinical (NIR) imaging will be performed on the study day and during the two follow-up visits.

In Part B, 10 mL of 50 μM AKRO-6qcICG in thermosensitive gel (corresponding to 1.15 mg), if well tolerated in Part A, will be topically applied onto all surgical cavity walls of all patients (superior, inferior, medial, lateral, and posterior (Figure 2)) after the standard-of-care (SOC) BCS resection. After 10 min of incubation and three washing steps with cold saline, the surgical cavity walls will be imaged with an intraoperative, clinical, open-system, NIR fluorescence-sensitive camera. The assessments will be performed in a standardised sequence and will increase the duration of the surgical procedure by a total of 15 min. At sites of fluorescence signal, biopsies will be performed to correlate the fluorescence signal to the presence of residual tumour cells. After a biopsy is taken, the surgical cavity wall will be imaged again. Additionally, in parallel AKRO-6qcICG imaging gel will be topically applied *ex vivo* onto the SOC resection specimen. After 10 min incubation and three washing steps with saline, the resected specimen will be imaged with a NIR fluorescence-sensitive camera system to detect any tumour-positive resection planes. All NIR fluorescence images will be correlated to final histopathology. On the day of surgery, blood samples will be collected for PK analysis. The complete schedule of assessments are depicted in Figures 3, 4.

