### Statistical analysis

Descriptive statistics will be depicted as mean (standard deviation, sd) or median (interquartile range, IQR). All statistical tests will be performed two-sided. A *p*-value of less than 0.05 will indicate a statistically significant difference. For part A and B, analysis of the safety and tolerability endpoints ((TE)(S)AEs, vital signs, ECG, and clinical laboratory tests) will be conducted with SAS 9.4 for Windows or newer (SAS Institute Inc., Cary, NC, USA). All (TE)(S)AEs will be listed and safety variable values outside the reference range will be flagged. Analysis of the pharmacokinetic endpoints (AUC_inf_, AUC_last_, CL/F, C_max_, t_1/2_, t_lag_, t_max_, Vz/F, Ae_last_, Ae_%_, CL/R) in plasma and urine will be conducted with R 3.6.1 for Windows or newer (R Foundation for Statistical Computing/R Development Core Team, Vienna, Austria, 2019). The individual PK parameters will be summarized per treatment group and, if applicable, will be presented graphically as boxplots. For Part B, the most recent version of SPSS (IBM, Armonk, New York, USA) will be used for statistical analysis of the exploratory NIR fluorescence imaging endpoints. Diagnostic accuracy analysis (including sensitivity, specificity, positive predictive value, and negative predictive value) will be performed based on a per resection wall (*in vivo* images)/per resection plane (*ex vivo* images) basis. To investigate differences in MFI between tumour tissue and adjacent healthy breast tissue on the surgical cavity walls and on the resection planes, the Wilcoxon signed-rank test will be used. The Spearman's correlation coefficient will be determined to investigate the correlation between the TBR of a fluorescent hotspot on a resection plane and the margin width at that location.

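### Part A gel strengths carry the wrong mass unit: mg/l is printed where the Part B dose requires mg/mL, a factor of 1000

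*Protocol article*

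**What the plan says.** In the protocol article, Intervention, the Part A conditions are named by molar strength, starting with "The four treatment conditions (AKRO-6qcICG 50" µM. Each active strength is followed by a mass equivalent: 50 µM is equated with "0.115 mg/l, AKRO-6qcICG 25" µM, and 25 µM with "0.0575 mg/l, vehicle (placebo), untreated".

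The next paragraph of the same section sets the Part B dose: "In Part B, 10 mL of 50" µM "AKRO-6qcICG in thermosensitive gel (corresponding to 1.15 mg), if well tolerated in Part A".

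The Study drug section describes the molecule but gives no molar mass: "AKRO-6qcICG is a small organic molecule whose structure is composed of both a NIR dye indocyanine green (ICG) and a non-fluorescent quencher moiety", bound to a dipeptide scaffold. The Statistical analysis section lists 11 pharmacokinetic parameters, some of which are calculated from the dose (the list ends "Vz/F, Ae_last_, Ae_%_, CL/R) in plasma and urine").

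**The concern.** Gel of the same agent at the same molar strength must have the same mass concentration in both parts. The article gives two values for 50 µM gel that differ by a factor of 1000, so at least one is wrong.

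This is a first-in-human study, and Part B goes ahead at 50 µM only if that strength is well tolerated in Part A. If gel were prepared to the printed mass figures, Part A would test strengths 1000-fold below those intended, and a clean tolerability result would say nothing about 50 µM. The product is reconstituted and diluted on the day of use and supplied in sealed syringes to a blinded investigator, so a wrong strength would be hard to notice at application. Separately, a Part A dose in mg derived from the printed figures would carry the same factor into every pharmacokinetic parameter that uses the dose.

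**Working it through.** **Inputs** (all from the protocol article, Intervention)
- Part A: 50 µM = 0.115 mg/l; 25 µM = 0.0575 mg/l.
- Part B: 10 mL of 50 µM gel = 1.15 mg.

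**1. Attempt to reproduce the Part A figure from the Part B dose.** Mass concentration = dose / volume.
- 1.15 mg / 10 mL = 0.115 mg/mL = 115 mg/L.
- Printed for the same 50 µM gel: 0.115 mg/L. The digits match and the unit does not; 115 / 0.115 = 1000.
- In reverse, 10 mL at 0.115 mg/L holds 0.115 × 0.010 = 0.00115 mg, not 1.15 mg.

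**2. Which figure is wrong?** Implied molar mass = mass concentration / molar concentration.

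| Source | Calculation | Implied molar mass |
|---|---|---|
| Part A, 50 µM as printed | 0.115×10⁻³ g/L / 50×10⁻⁶ mol/L | 2.3 g/mol |
| Part A, 25 µM as printed | 0.0575×10⁻³ g/L / 25×10⁻⁶ mol/L | 2.3 g/mol |
| Part B | 1.15×10⁻³ g / (50×10⁻⁶ mol/L × 0.010 L) | 2,300 g/mol |

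A single carbon atom is 12 g/mol, so 2.3 g/mol is impossible for a dye and a quencher on a dipeptide. The article states no molar mass, but the conclusion does not depend on one. Over an assumed range of 500 to 3,000 g/mol, 50 µM is 25 to 150 mg/L, and no value in that range comes near 0.115 mg/L.

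**3. Corrected values at 2,300 g/mol.**
- 50 µM: 50×10⁻⁶ × 2,300 = 0.115 g/L = 0.115 mg/mL, and 10 mL then holds 1.15 mg, as Part B states.
- 25 µM: 25×10⁻⁶ × 2,300 = 0.0575 g/L = 0.0575 mg/mL (57.5 mg/L).

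The printed digits are right in mg/mL at both strengths, and the 2:1 ratio holds. This is one unit slip, made twice.

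**4. What the printed mass figures would mean if followed.**
- 0.115×10⁻³ g/L / 2,300 g/mol = 5.0×10⁻⁸ mol/L = 50 nM.
- 0.0575×10⁻³ g/L / 2,300 g/mol = 2.5×10⁻⁸ mol/L = 25 nM.

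**5. Pharmacokinetic parameters, if a Part A dose were derived from the printed figures.** Each volunteer receives both active strengths. Both carry the same factor, so the total dose would also be 1000-fold too low.
- CL/F = dose / AUC: 1000-fold too low.
- Vz/F = dose / (AUC × λz): 1000-fold too low.
- Ae% = 100 × Ae / dose: 1000-fold too high.
- AUC_inf, AUC_last, C_max, t½, t_lag, t_max, Ae_last and CL/R (read as renal clearance, Ae / AUC) do not use the dose: 8 of the 11 are unaffected.

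**The case against.** The strongest reply is that the operative strength is the molar one. Each condition is named in µM, the mass figure is only an equivalent beside it, and Part B again specifies 50 µM with a consistent total dose. This stands: the bridge from Part A to Part B at 50 µM is intact, and the point should not be read as showing that a different gel strength is planned.

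The consequences are also conditional. Making 50 nM gel would mean disregarding the µM value printed alongside. The product is made in a clinical pharmacy department under cGMP, and a journal article is not shown to be a preparation instruction. The article gives no gel volume per blister, so a Part A dose in mg cannot be calculated from it alone, whichever unit is used; any pharmacokinetic analysis must draw on a dosing record that is not shown. The article itself, under Expected limitations and difficulties, doubts that a systemic concentration will be detectable, in which case these parameters may not be estimable. These points stand too. They limit the likelihood of harm but do not make the printed figure correct.

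A slip this visible may be less likely to spread unnoticed than a plausible wrong number. That is a reason to expect an easy correction, not a reason to leave the figure in place. A text-extraction fault is unlikely, because mg/l appears at both strengths while mL is preserved elsewhere in the article.

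**Conclusion.** The concern holds. Both Part A mass equivalents are wrong by a factor of exactly 1000, and the error lies in their unit. The contradiction follows from the article's own figures and needs no outside value. Placing the error in Part A rather than Part B rests only on 2.3 g/mol being physically impossible. The value of 2,300 g/mol is inferred from the Part B dose and is not stated in the article.

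It should be fixed, because it concerns the printed strength of a first-in-human product whose Part A tolerability decides whether the Part B dose is given. It changes no endpoint, sample size, randomisation or planned analysis. Harm would arise only if someone worked from the mass figure instead of the µM figure, and the article does not show whether the pharmacy documents contain the same slip.

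**What to change.** In the Intervention section, change the unit from mg/l to mg/mL at both Part A strengths, so that 50 µM = 0.115 mg/mL and 25 µM = 0.0575 mg/mL. First confirm the molar mass of about 2,300 g/mol against the pharmacy record. Before any syringe is prepared, check that the pharmacy and dosing documents, including whatever supplies the Part A dose for the pharmacokinetic analysis, do not repeat the slip.

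The cost is a one-line correction and one document check. The molar strengths, the Part B dose, the sample size and the study procedures stay as they are.

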Currently, most tumour-targeted contrast agents for fluorescence-guided BCS are administered intravenously prior to surgery (16, 17). Alternatively, contrast agents could be topically applied to the surgical cavity after tumour resection, offering fast visualization of residual tumour, smoother integration into the surgical workflow, lower chances of systemic side effects, and improved cost-effectiveness. Several topical fluorescent probes have been tested *in vivo* in a preclinical setting and *ex vivo* on resected human breast cancer specimens, but these agents were not able to adequately distinguish malignant from benign breast tissue (18, 19). A promising topically applied contrast agent for fluorescence-guided BCS is AKRO-6qcICG, a fluorescently quenched, protease-activatable probe composed of indocyanine-green (ICG) and a NIR quencher conjugated to a peptide Cbz-Phe-Lys core (20). It functions as a “smart” probe, producing a fluorescent signal only when processed by tumour-associated enzymes – cathepsin B, L, and S - which are highly upregulated in breast cancer compared to healthy tissue (21, 22). AKRO-6qcICG leverages a latent lysosomotropic effect (LLE), accumulating fluorescent fragments in lysosomes, enhancing signal strength and duration (20). In an *ex vivo* validation study AKRO-6qcICG, formulated in a thermosensitive gel, effectively differentiated between human breast cancer and adjacent healthy tissue and allowed for the detection of tumour-positive resection margins with a high sensitivity and considerable specificity (23, 24). However, due to the soft, pliable nature of a resected breast cancer specimen, its geometry does no longer accurately correspond to that of the resection cavity. Consequently, correlating an *ex vivo* detected tumour-positive resection margin to the *in vivo* location of the residual tumour that needs to be excised can be very difficult. Combining the *ex vivo* margin assessment with the *in vivo* detection of residual tumour tissue on the surgical cavity walls seems to be the most promising approach. Therefore, we propose the SPRAYDYE-study: ‘*Fa**S**t intrao**P**erative **R**esection margin **A**ssessment in breast-conserving surgery using a topicall**Y** applie**D**, fluorescentl**Y**-quenched, protease-activatable imaging ag**E**nt’.*

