### Sample size

Six healthy volunteers and 16 breast cancer patients will be enrolled. As this is an exploratory study, the sample size is not based on formal statistical considerations. The proposed sample size will be sufficient to test the hypothesis.

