#### Exploratory outcomes

In Part B, exploratory outcomes include the analysis of the NIR fluorescence images of the surgical cavity walls. Diagnostic accuracy of topically applied AKRO-6qc-ICG will be determined by categorizing each surgical cavity wall (*in vivo)* and resection plane (*ex vivo*) as true positive (fluorescent and tumour positive), true negative (not fluorescent and tumour negative), false positive (fluorescent and tumour negative) or false negative (not fluorescent and tumour positive). Additionally, the signal-to-background ratio (SBR) of fluorescent areas will be calculated.

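### Cavity walls are biopsied only where they fluoresce, so in vivo per-wall sensitivity and negative predictive value rest on different references for bright and dark walls and are biased, most likely upward

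*Protocol article*

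**What the plan says.** The Intervention section of the protocol article gives one rule for sampling the cavity in Part B: "At sites of fluorescence signal, biopsies will be performed to correlate the fluorescence signal to the presence of residual tumour cells". It describes no sampling of walls that stay dark. The gel is applied to five walls ("superior, inferior, medial, lateral, and posterior"), and the Sample size section fixes 16 patients, so about 80 walls are at issue.

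The Exploratory outcomes section sorts each cavity wall into four cells, one of which is "false negative (not fluorescent and tumour positive". The Statistical analysis section then says: "Diagnostic accuracy analysis (including sensitivity, specificity, positive predictive value, and negative predictive value) will be performed based on a per resection wall".

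The only other reference named is a general sentence in the Intervention section: "All NIR fluorescence images will be correlated to final histopathology". It does not say which tissue supplies the tumour status of a dark cavity wall. On the resected specimen, the Introduction says that "its geometry does no longer accurately correspond to that of the resection cavity", and adds that tracing a positive specimen margin back to its place in the cavity can be very difficult.

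**The concern.** Sensitivity and negative predictive value need the tumour status of the walls that did not fluoresce. Under the stated rule the test under study decides which walls yield tissue. This is partial verification if dark walls have no reference, and differential verification if they are judged from the specimen while bright walls are judged by biopsy.

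The two groups are then treated unequally. Residual tumour behind a clean specimen margin is a true positive if the wall fluoresces and would be scored a true negative if it does not.

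At stake is the second half of the protocol's hypothesis, that the agent can detect residual breast cancer in the cavity. In vivo sensitivity is the figure that speaks most directly to that claim. The section on expected limitations discusses too few tumour-positive walls and difficult camera access, but not the verification of dark walls.

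**Working it through.** The article gives no accuracy target and no formal sample-size basis, so there is no figure of its own to reproduce. The check asks how far the verification scheme can move the estimates.

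**Inputs from the article.** 16 patients × 5 walls = 80 walls.

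**Assumed inputs (not in the article).** Tumour in 10% of walls, true sensitivity 70%, true specificity 80%; wider ranges follow. Let f be the share of tumour-positive dark walls that are recognised as positive by some route, and g the share of truly clear dark walls that face a positive specimen margin. Biopsy status of bright walls is taken as correct.

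**True table**
- Walls with tumour: 80 × 0.10 = 8, so TP = 8 × 0.7 = 5.6 and FN = 2.4.
- Walls without tumour: 72, so FP = 72 × 0.2 = 14.4 and TN = 57.6.
- True NPV = 57.6/60 = 96.0%.

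**Formulas**
- Apparent sensitivity = TP / (TP + f·FN + g·TN)
- Apparent NPV = 1 − (f·FN + g·TN) / (FN + TN)

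**Results against true values of 70% and 96.0%**

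| f | g | Apparent sensitivity | Apparent NPV |
|---|---|---|---|
| 0 | 0 | 5.6/5.6 = 100% | 100% |
| 0.25 | 0 | 5.6/6.2 = 90.3% | 99.0% |
| 0.5 | 0 | 5.6/6.8 = 82.4% | 98.0% |
| 0.5 | 2% | 5.6/7.952 = 70.4% | 96.1% |
| 0.5 | 5% | 5.6/9.68 = 57.9% | 93.2% |
| 1 | 0 | 5.6/8 = 70.0% | 96.0% |

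**Other assumed values, g = 0.** At f = 0, sensitivity and NPV are 100% at every true sensitivity tried (50%, 70%, 90%), while the true NPV runs from 86.5% to 99.3% over a tumour prevalence of 5% to 20%. At f = 0.25, true sensitivities of 50%, 70% and 90% appear as 80%, 90% and 97%. At f = 0.5 they appear as 67%, 82% and 95%.

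**Where the direction turns.** The two errors cancel when g·TN = (1 − f)·FN. At f = 0.5 this gives g = 1.2/57.6 = 2.1%, or 1.2 walls. Above that share, sensitivity is understated.

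**Specificity.** With g = 0 it moves from the true 80% to at most 82.2% (prevalence 20%, true sensitivity 50%, f = 0: 59.2/72). At f = 0.5 and g = 5% in the main table it is 55.92/70.32 = 79.5%.

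**PPV.** Numerator and denominator both come from biopsied fluorescent sites, so neither f nor g enters.

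**Specimen plane as the reference for all walls.** Apply f = 0.5 and g = 5% to bright and dark walls alike. Margin-positive bright walls are 2.8 + 0.72 = 3.52 and margin-positive dark walls are 1.2 + 2.88 = 4.08. Sensitivity is 3.52/7.60 = 46.3%, further from the true 70% than the mixed reference (57.9%). One common reference removes the unequal treatment, but what it measures is agreement with the specimen margin.

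**The case against.** The strongest reply is that the sentence on correlating all images with final histopathology covers images of dark walls too, and that a false-negative cell is provided. The Abstract treats a positive specimen margin as implying residual tumour. Using specimen margin status for every wall is compatible with the text and may be what is intended. The article is condensed, and the full protocol or analysis plan may name the reference for each wall.

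Much of this stands. A reader might infer that sensitivity is bound to come out at 100%, or is inflated by design. The article does not support that: nothing says that biopsy is the sole reference or that unbiopsied walls count as clear. The 100% figure is a limiting case, and the working shows that specimen margins can also push sensitivity below its true value. A reader might also infer that a high negative predictive value is meant to justify leaving dark walls unresected in a later trial. No such trial is mentioned; the stated use is to guide additional resection.

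What does not fall away is the sampling rule, which is stated and not merely left open. It settles which tissue will exist, and no later analysis plan can recover the status of an unsampled wall. The general histopathology sentence leads at best to the specimen, whose poor match to the cavity the Introduction itself describes.

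**Conclusion.** The point holds in a limited form. As the article stands, in vivo sensitivity and negative predictive value per wall would combine a direct reference for bright walls with an indirect one, or none, for dark walls. They are biased, most likely upward, because tumour in a dark wall behind a clean margin goes unseen. That direction is a judgement and not a certainty. With true sensitivity assumed at 70%, the scenarios tabulated run from 58% to 100%; prevalence, sensitivity, specificity, f and g are all assumptions. Specificity is little affected, and the biopsy-based positive predictive value is sound.

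Severity is moderate. The accuracy endpoints are exploratory, the study is a 16-patient pilot, and the primary safety outcome is untouched. The point would fall away if the full protocol provides cavity histology for dark walls, which the article does not describe.

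**What to change.** In the Exploratory outcomes and Statistical analysis sections, before data are collected:

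1. Make the per-site positive predictive value the main in vivo accuracy measure: tumour-positive biopsies divided by all biopsied fluorescent sites.
2. Do not count a dark, unbiopsied wall as a verified true negative.
3. State that in vivo sensitivity and negative predictive value against cavity histology are not estimable under this biopsy rule.
4. If sensitivity, specificity and negative predictive value are still reported per wall, use one reference, the facing specimen plane, in the same way for bright and dark walls. Label the result as agreement with specimen margin status, not as detection of residual cavity tumour. Show walls where biopsy and specimen margin disagree in a separate table; otherwise biopsy-proven tumour behind a clean margin would be scored only as a false positive.

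The cost is revised wording and one extra table. No extra tissue is needed. The downside is that the in vivo accuracy claims become narrower and less favourable, and that the specimen plane remains an imperfect stand-in for the cavity wall.
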